## 7.0 TREATMENT PLAN

### 7.1 Sorafenib Dose Levels and Definition of Dose-Limiting Toxicity

Evaluation for loco-regional toxicity from therapy will occur daily (excluding weekends and holidays) while patient is receiving RT (**see section 10.1 for study calendar**) and then biweekly during the rest period following completion of RT prior to surgical resection. Evaluation for generalized/systemic toxicity (e.g. hypertension, myelosuppression, etc.) will occur weekly (**see section 10.1 for study calendar**) during the treatment phase and then biweekly during the rest phase of the study. Patients will maintain a pill diary so that a record of self-administered medications will be available.

| Dose Level | Sorafenib          | Radiation       |
|-------------------|---------------------------|------------------------|
| 1                 | 200 mg twice daily        | 200 cGy x 25 fractions |
| 2                 | 200 mg q am
400mg q pm | 200cGy x 25 fractions  |
| 2                 | 400 mg twice daily        | 200 cGy x 25 fractions |

A traditional dose-escalation design will be used to determine the MTD of sorafenib combined with radiotherapy. The MTD is defined as the dose that produces dose limiting toxicity (DLT) in 33% of patients. Three patients will be enrolled per dose level, with escalation to the next dose level if no dose-limiting toxicity (DLT) is observed. If one DLT is observed, the dose level will be expanded to a total of 6 patients, and escalation will occur if no more than one DLT is observed among the 6 patients. If 2 or more out of 3 patients, or 3

or more out of 6 patients experience DLT, the study will be terminated or dose reduced to the previous dose level. Dose level escalation will be determined based on DLTs observed from start of treatment until date of surgery, but DLTs will be monitored in the postoperative period, and dose de-escalation may occur if excess late DLTs are observed.

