DLT is defined as: grade 4 anemia, grade 4 neutropenia lasting > 7 days, grade 3-4 thrombocytopenia with clinically significant bleeding or grade 4 thrombocytopenia lasting > 5 days, and grade 3-4 non hematologic toxicity (except: nausea/vomiting that responds to anti-emetic therapy; grade 3 neutropenic fever lasting  $\leq 5$  days; grade 3 encephalopathy lasting  $\leq 2$  days; grade 3-4 hypokalemia, hypophosphatemia, hypomagnesemia, hypocalcemia unless requiring hospitalization; grade 3 diarrhea controlled with medication within 2 days; and grade 3 grade hypertension that is adequately controlled with medication (BP <150/100)).

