|                    |                                  |                                  | a second grade 3 toxicity, withhold dose until toxicity is grade $\leq 1$ , then reduce one dose level and resume treatment.                                                                                                                               | discontinue at the discretion of the principal investigator.                                                                                                                                                      |
| Hematologic | Continue at the same dose level. | Continue at the same dose level. | Withhold dose until toxicity is grade $\leq 2$ , then resume treatment at the same dose level. If patient experiences a second grade 3 toxicity, withhold dose until toxicity is grade $\leq 2$ , then reduce dose to 400 mg p.o. qd and resume treatment. | Withhold dose until toxicity is grade $\leq 2$ , then reduce dose to 400 mg p.o. qd and resume treatment, or discontinue at the discretion of the principal investigator after discussion with study supporter. . |

\*Patients who develop grade 3 fever/chills, grade 3 elevation of hepatic transaminases with ALT and AST  $<10\times$  ULN, grade 3 hyperlipasemia or hyperamylasemia without clinical or other evidence of pancreatitis, grade 3 leukopenia, or grade 3/grade 4 lymphopenia may continue study treatment without interruption at the discretion of the investigator.

Because certain grade 3-4 adverse events may occur with radiotherapy, the above table should be modified for these adverse events as defined below (unless the adverse events are definitely attributable only to sorafenib, in which case refer to above table). Attribution to sorafenib at least in-part should be present in order to justify sorafenib dose-reduction:

- Neutropenia – Grade 3 or Grade 4 lasting  $\leq 7$  days: no action. Grade 4 lasting  $>7$  days: refer to table above
- Neutropenic Fever – Grade 3 lasting  $\leq 5$  days: no action. Grade 3 lasting  $>5$  days or Grade 4: refer to table above
- Leukopenia – No dose reduction
- Thombocytopenia -- Grade 3: no action. Grade 4: refer to table above. Grade 3-4 with clinically significant bleeding: treat as Grade 4
- Anemia – Grade 3: no action. Grade 4: refer to table above
- Nausea/Vomiting – Per above table, only if persistent Grade 3-4 despite maximal anti-emetic adjustment
- Fatigue – Grade 3: no action. Grade 4: refer to table above.

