## 8.0 AGENT FORMULATION AND PROCUREMENT

### 8.1 Sorafenib (Nexavar)

**Availability:** Sorafenib will be supplied for this study

**Product description:** Sorafenib 200 mg is supplied as round, biconvex, red-film-coated tablets, debossed with the 'Bayer cross' on one side and '200' on the other side.

The tablets contain sorafenib tosylate equivalent to 200 mg of the free base sorafenib, and the excipients croscarmellose sodium, microcrystalline cellulose, hypromellose, sodium lauryl sulfate, and magnesium stearate. The film-coat consists of hypromellose, polyethylene glycol, titanium dioxide and red iron oxide. The film coating has no effect on the rate of release of the active sorafenib tosylate. Study Drug can be supplied as sorafenib 200 mg commercial tablets in bottles of 140 tablets with a product identification label affixed or as commercial Nexavar in bottles of 120 tablets.

**Storage requirements:** Do not store above 25°C (77°F). Store in the original package.

**Stability:** The current shelf life is 36 months.

**Route of administration:** Orally.

**Expected adverse events:** The following additional drug-related adverse events and laboratory abnormalities were reported from clinical trials of sorafenib in 1286 cancer patients who received sorafenib as monotherapy (*very common* 10% or greater, *common* 1 to less than 10%, *uncommon* 0.1% to less than 1%):

Cardiovascular: *Very Common:* hypertension *Uncommon:* hypertensive crisis, myocardial ischemia and/or infarction

Dermatologic: *Very common:* hand-foot skin reaction *Common:* , dry skin, pruritus *Uncommon:* folliculitis, , erythema multiforme

Digestive: *Very common:* anorexia, nausea, diarrhea, abdominal pain, weight loss *Common:* constipation, vomiting, hyperamylasemia, hyperlipasemia *Uncommon:* pancreatitis. Note that elevations in lipase are common; a diagnosis of pancreatitis should not be made solely on the basis of abnormal laboratory values

General Disorders: *Very common:* fatigue *Uncommon:* hemorrhage

Hematologic: *Common:* leukopenia, lymphopenia, thrombocytopenia *Uncommon:* INR abnormal

Hypersensitivity: *Uncommon:* hypersensitivity reactions (including skin reactions and urticaria)

Metabolic and Nutritional: *Very common:* hypophosphatemia *Common:* transient increases in transaminases *Uncommon:* hypothyroidism

Musculoskeletal: *Common:* arthralgia, myalgia

Reproductive: *Uncommon:* gynecomastia

Respiratory: *Uncommon:* hoarseness, rhinorrhea

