| Doctor's Visit, Measure BP        |  |                                                                                                              |                                                                                                              |                                                                                                              |                                                                                                              |                                                                                                              |  |  |  |  |
| Procedures                 |                                     |                                                                                                                                                 |                                                                                                                                                 |                                                                                                                                                 |                                                                                                                                                 |                                                                                                                                                 |                                     |                                     |                                     |                                     |

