#### 10.4.1 Toxicities and Adverse Events

Toxicities and adverse events will be assessed at each visit using the NCI Common Toxicity Criteria for Adverse Events v3.0 (<http://ctep.cancer.gov/reporting/ctc.html>). **Acute and long-term radiation toxicity must be graded at each visit for the following CTCAE categories:**

- 1) Dermatologic/Rash: Dermatitis associated with radiation**
- 2) Musculoskeletal/Soft Tissue: Extremity (as appropriate for location of tumor)**
- 3) Musculoskeletal/Soft Tissue: Fibrosis—deep connective tissue**

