### 10.4.4 Schedule of Events

|                                               | Prior to
Registration | Prior to Day 1
of Treatment | Time of Pre-
Surgical
Restaging* | Post
Treatment
Follow-up |
|-----------------------------------------------|--------------------------|--------------------------------|----------------------------------------|--------------------------------|
| Tests & Observations        |                          |                                |                                        |                                |
| History and Progress Notes                    | X                        | X                              | X                                      | X                              |
| Physical Examination                          | X                        | X                              | X                                      | X                              |
| Pulse, Blood Pressure**                       | X                        | X                              | X                                      | X                              |
| Height/Weight                                 | X                        |                                |                                        |                                |
| Performance Status                            | X                        | X                              | X                                      | X                              |
| Treatment Toxicity
Assessment              |                          | #                              | #                                      | #                              |
| Pathology Review                              | ##                       |                                | ##                                     |                                |
| Laboratory Studies              |                          |                                |                                        |                                |
| CBC, Differential, Platelets                  | X                        |                                | X                                      | PRN                            |
| Serum Chemistries***                          | X                        |                                | X                                      | PRN                            |

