### 10.5 Specimen Submission for Molecular Correlative Studies

With the patient's consent, tissue and blood specimens will be submitted as outlined below.

- Paraffin-embedded tissue blocks or slides from the time of diagnosis (prior to therapy) and at the time of surgical resection will be submitted for expression of relevant molecular targets. 1-2 paraffin-embedded tissue blocks containing formalin-fixed tumor tissue should be submitted for evaluation and expression of mutations in relevant molecular pathways. Paraffin blocks should be processed according to standard institutional protocols. If blocks are unavailable, 16 unstained slides are acceptable alternatives.
- Two blood specimens will be collected from each patient prior to treatment (2 x 10 mL). Subsequent blood specimens (1 x 10 mL) will be collected at selected intervals as indicated in the study calendar (see section 10.1, weeks 2, 6, 9, and end of study). In the event that a patient is removed from the study, a blood specimen (approximately 10 mL) will be obtained at the time the patient is removed from protocol treatment.

One blood specimen should be collected in a 10 mL purple-top (EDTA) tube, inverted several times, and placed on wet ice until centrifugation. The tube should be centrifuged as soon as possible at approximately 1,000 to 1,500 rpm for 10 minutes. Plasma should be removed and placed in 1 mL aliquots in labeled cryotubes. Buffy coat cells should be separately removed and placed in labeled cryotubes. All specimens must be labeled with protocol number, patient registration number, and date of specimen collection. All tubes are then to be frozen (snap frozen with liquid nitrogen if possible) and stored at -70°C until shipped to the laboratory on dry ice as detailed below.

The second blood specimen should be collected in a 10 mL red-top tube, allowed to clot at room temperature for 30 minutes, and placed on wet ice until centrifugation. The tube should be centrifuged at 3000 rpm for 10 minutes. Serum should be removed and placed in 1 mL aliquots in labeled cryotubes. All specimens must be labeled with protocol number, patient registration number, and date of specimen collection. All tubes are then to be frozen (snap frozen with liquid nitrogen if possible) and stored at -70°C until shipped to the laboratory on dry ice as detailed below.

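### Section 7.1 promises weekly evaluation of myelosuppression on treatment, but the calendar it cites schedules blood tests in only one of the five treatment weeks, so laboratory DLTs can be missed or left untimed

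*Protocol*

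**What the plan says.** Protocol section 7.1 sets the frequency of systemic evaluation on treatment: "Evaluation for generalized/systemic toxicity (e.g. hypertension, myelosuppression, etc.) will occur weekly". It cites section 10.1 for the schedule and moves to a biweekly rhythm in the rest phase. Section 10.4.1 adds: "Toxicities and adverse events will be assessed at each visit using the NCI Common Toxicity Criteria for Adverse Events v3.0".

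In calendar 10.1 the row "Doctor's Visit, Measure BP" is ticked in every treatment week. The blood test row is ticked before study, in week 2, in the two rest columns (Week 6-8 and Week 7-9) and at end of study. It is blank in weeks 1, 3, 4 and 5.

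Section 10.5 reads the calendar in the same way when it places the correlative specimens: "at selected intervals as indicated in the study calendar (see section 10.1, weeks 2, 6, 9, and end of study". In 10.4.4 the row "CBC, Differential, Platelets" is marked before registration, at pre-surgical restaging, and as needed in follow-up. The chemistry row is marked likewise. That table has no on-treatment column, and its weekly footnote covers blood pressure only.

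In the DLT definition of 7.1, the neutrophil and platelet criteria depend on duration or bleeding: "grade 4 neutropenia lasting > 7 days, grade 3-4 thrombocytopenia with clinically significant bleeding or grade 4 thrombocytopenia lasting > 5 days". Anemia of grade 4 also counts, as do non-hematologic events of grade 3 or 4 apart from listed exceptions. Transaminase rises are not among the exceptions.

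**The concern.** Myelosuppression cannot be graded without a blood count. The text therefore implies a count in each treatment week, while the calendar that it names schedules one in five weeks. Staff can follow either part of the protocol and believe that they comply, yet collect different DLT data.

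The Phase I result rests on those data: 3+3 escalation counts the DLTs observed from the start of treatment to surgery. A clinically silent laboratory DLT in weeks 3-5 may never be seen. A grade 4 count found in week 2 has no scheduled repeat before week 6, so the duration limits in the DLT definition cannot be judged from the calendar. The error runs one way, because a missed DLT can only make a dose level look safer.

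**Working it through.** **1. Counts on treatment.** Treatment lasts about 35 days (7.4), which is weeks 1-5. Weekly evaluation as in 7.1 implies 5 counts. Calendar 10.1 gives 1, in week 2. Section 10.4.4 adds 0.

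**2. Is the blank real?** Section 10.5 independently lists weeks 2, 6, 9 and end of study from the same calendar, so the ticks are as intended. Where the protocol wants weekly monitoring it says so, as for blood pressure (7.2.3 and the 10.4.4 footnote) and INR in patients on warfarin (6.1). No section schedules a weekly count.

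**3. Interval if the row is safety blood.** Week w covers days 7(w-1)+1 to 7w, so week 2 is days 8-14 and week 6 is days 36-42.
- Shortest interval between draws: 36 - 14 = 22 days, with 21 count-free days (15 to 35).
- Longest, with the next draw in week 6: 42 - 8 = 34 days, with 33 count-free days (9 to 41).
- Longest, if the Week 6-8 column is used to its last day (day 56): 56 - 8 = 48 days.

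**4. If the row is research blood.** Section 10.5 attaches these same weeks to correlative specimens. On that reading the 22-34 days do not apply, and the number of scheduled safety counts between the pre-treatment sample and the rest phase is zero.

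**5. Duration limits.** Grade 4 neutropenia counts as a DLT only beyond 7 days, and grade 4 thrombocytopenia only beyond 5 days. A single draw shows that a value was grade 4 on one day and nothing about how long it lasted. Weekly draws alone do not settle this either: with draws 7 days apart, a 6-day episode can contain at most one of them. A repeat rule is needed as well as weekly counts.

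**6. How common might silent laboratory DLTs be?** Section 8.1 places "leukopenia, lymphopenia, thrombocytopenia" and transient transaminase increases at 1 to less than 10% of patients on monotherapy. It gives no grade or duration and lists neither neutropenia nor anemia. The share of DLTs that would be laboratory-only, and their length, are not in the protocol, so no detection rate or escalation probability can be calculated without inventing inputs.

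**The case against.** The strongest reply is that the protocol already requires the counts. Section 7.1 names myelosuppression and says weekly; the grid merely lacks ticks, and a team that follows the text loses nothing. This is true, but it restates the contradiction: 7.1 sends the reader to the grid, and the grid says otherwise.

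A second reply is that 7.2.4 already presupposes serial counts. It asks for no action on grade 4 neutropenia of 7 days or less, and for withholding until grade 2 or below in other cases. Neither instruction can be carried out without repeat values. That stands in part, but 7.2.4 gives no interval.

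Third, the consequences are bounded. Unscheduled counts are not forbidden, and toxicity that shows clinically would be noticed at the weekly visits. Section 7.1 excludes several electrolyte abnormalities from DLT unless they require hospitalization. For grade 3 transaminase rises with ALT and AST below 10 times ULN, among other values, 7.2.4 says patients "may continue study treatment without interruption at the discretion of the investigator", so few dose holds would be lost. The dose cannot exceed 400 mg bid (4.0), late DLTs can trigger de-escalation (7.1), and Phase II pauses after 10 patients. All of this stands and limits the harm. The Phase II pause is not a fully independent safeguard, however: it counts grade 3 or higher events, and silent laboratory events would be undercounted there through the same calendar.

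A reader might go further and infer that DLTs will be missed, that the MTD is invalid, or that escalation becomes more likely by some stated amount. The documents support none of these. They show that the calendar permits a miss and fixes its direction, and they give no basis for its frequency.

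**Conclusion.** The contradiction between 7.1 and calendar 10.1 is real, and 10.4.4 does not repair it. One blood test is scheduled in five treatment weeks where the text implies five. If the row is safety blood, the next draw comes 22-34 days after the week 2 draw on the week 6 timing of 10.5, and up to 48 days on the calendar's own column. If the row is research blood, no safety count is scheduled on treatment.

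The DLTs exposed are grade 4 anemia, grade 4 neutropenia beyond 7 days, grade 4 thrombocytopenia beyond 5 days, and grade 3-4 transaminase rise, where these cause no symptoms. Any loss biases toward escalation by an amount that cannot be derived here. The conclusion assumes only that some staff would work from the calendar rather than from the text. The matter should be corrected because the correction is simple and protects the Phase I endpoint, but it does not by itself undermine the design.

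**What to change.** - **10.1:** tick CBC with differential and platelets, plus the comprehensive metabolic panel, weekly in weeks 1-5 and every two weeks in the rest phase until surgery. This reads biweekly in 7.1 as every two weeks, and the text should say so.
- **10.4.4:** add a footnote to the CBC and chemistry rows stating that sampling during treatment and rest follows 10.1.
- **10.1 and 10.5:** give the correlative draws their own calendar row, so that research and safety blood cannot be confused.
- **7.1:** state that any grade 4 neutrophil or platelet value is repeated at a fixed short interval, for example every 2-3 days, until it is below grade 4. The 7-day and 5-day limits can then be judged.

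**Cost.** On treatment, 5 - 1 = 4 extra draws per patient at visits already scheduled, or 4 x 30 = 120 to 4 x 35 = 140 draws over the planned 30-35 patients. If the week 2 blood is research blood, a safety tube can be added to that draw, so the extra draws remain 4. In the rest phase, 0-2 more per patient, depending on whether surgery falls near day 50 or day 90. Repeat counts arise only after a grade 4 neutrophil or platelet value.

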|  | 
tumor vasculature leads to disordered/poorly regulated tumor perfusion which appears to normalize following delivery of anti-angiogenic agents. This, in turn, allows improved delivery of and susceptibility to cytotoxic agents, which is particularly important with RT since hypoxia is a key mechanism of resistance to this modality. Preliminary clinical data in rectal cancer and malignant brain tumors have demonstrated promising results from the combination of anti-angiogenic agents and RT with respect to downstaging of the primary tumor, local tumor control, and improved progression-free survival. Angiogenic factors are upregulated in patients with STS, and anti-angiogenic agents demonstrate activity against STS in the metastatic setting.
 
Consequently, we propose to evaluate preoperative combined modality sorafenib and conformal RT in patients with STS of the extremity in this prospective trial. Key endpoints will be safety and toxicity in the Phase I trial and pathological response in the Phase II trial. Additional endpoints will include molecular and functional imaging correlative studies of biomarkers of response and resistance to treatment. Enrollment into Phase I will be completed prior to the initiation of phase II.
 
We hypothesize that this combination will be safe and will increase pathologic necrosis within the primary tumor at the time of surgical resection, translating into reduced volume of resected tissue, improved local disease-control, and ultimately improved disease-free survival. Functional imaging studies (dynamic contrast-enhanced MRI) and molecular examination of pre- and post-treatment tumor tissue and serum will allow correlation of changes in tumor blood flow, hypoxia transcription factors, phosphorylated ERK, and angiogenic markers to the degree of tumor necrosis following treatment with preoperative sorafenib and radiotherapy.
 |

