### 1.2 Surgery with External Beam Radiotherapy

For patients with localized STS amenable to resection with curative intent, surgical treatment in combination with RT results in local disease control in 76% to 92% of patients with successful limb preservation, i.e. avoidance of amputation, in 90 to 95% of patients whose tumors are located on the extremity. Although function-sparing surgery combined with RT represents a significant advance for patients with STS, this approach still requires total en bloc excision of the primary tumor with a goal of 2 centimeters of normal tissue around the tumor in all directions. These operations risk significant morbidity for the patient.

An important component of local therapy in STS is adjuvant RT. Adjuvant RT for patients with STS of the extremity has been shown to reduce local recurrence rates by 20 to 25% relative to radical resection alone. The timing of RT administration (preoperative versus postoperative) has been compared in a randomized clinical trial. This trial demonstrated that preoperative RT was associated with a statistically significant increase in perioperative wound complications (35% vs. 17%). Conversely, at a median follow-up of 6.9 years, preoperative RT was associated with a statistically significant decrease in long term complications, such as joint fibrosis, joint stiffness, and extremity edema (23% vs. 36%). Although these data have been interpreted in different ways by different investigators, advocates of preoperative radiotherapy maintain that the data favor the preoperative administration of RT since perioperative wound complications are generally reversible whereas late complications of radiotherapy are generally irreversible. Furthermore, although considered a secondary endpoint of the trial, overall survival was statistically improved in the patients who received preoperative radiotherapy (85% vs. 75% at 3 years,  $P=0.048$ ). Although these secondary survival data regarding neoadjuvant RT should be viewed with caution, it is reasonable to hypothesize that neoadjuvant RT in combination with novel systemic agents may improve both local and distant disease-control in patients with STS.

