#### 4.0 ACCRUAL GOAL

- Phase I— Dose-escalation schedule comprising 6 to 12 patients (see schema). This sample size is based on a traditional 3+3 cohort design with escalating doses of sorafenib in combination with 50 Gy of conformal radiotherapy delivered in 25 fractions (200 cGy per fraction). Based on preclinical data regarding the radiobiology of sorafenib, sorafenib will be initiated at a dose of 200 mg twice daily, followed by 200 mg Q AM/400 mg Q PM for the 2nd cohort, followed by 400 mg bid for the 3rd cohort. Since 400 mg bid is the well established MTD for sorafenib monotherapy in patients with renal cell carcinoma and hepatocellular carcinoma, the dose will not be escalated above this level even if DLT is not observed. Dose level escalation will be determined based on DLTs observed from initiation of sorafenib/RT until time of surgery.
- Phase II— anticipated number of 25 patients will be enrolled depending on phase I result. Anticipating an improvement in near-complete pathological response ( $\geq 95\%$  tumor necrosis) from 0% with RT alone to 33% with combined sorafenib and RT, we will have an 80% power to detect this difference if we accrue 25 patients, assuming a type I error rate of 5%.

Total target accrual is 30-35 patients depending on results of dose-escalation schedule from Phase I of trial.

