Resectability will depend upon the judgment of the operating surgeon. For the extremities, resection must be limb salvage procedure. Extremity patients who are not resectable without amputation may be amputated. Unresectable tumors may be palliated with surgery, chemotherapy, or additional radiation therapy. These patients will be taken off protocol.

**Note that documentation of wound complications is an integral part of this clinical trial. Wound complications are defined in section 10.4.2 and must be accurately recorded and reported.**

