## 13.0 STATISTICAL CONSIDERATIONS

### 13.1 Primary Objective

#### 13.1.1 Phase I Trial

To determine the maximally tolerated dose (MTD) of the antiangiogenic agent sorafenib in combination with preoperative conformal radiotherapy for soft tissue sarcomas of the extremities and the body wall, high grade > 5 cm in diameter and low grade > 8 cm. A traditional dose-escalation design will be used to determine the MTD of sorafenib combined with radiotherapy. 3-6 patients will be evaluated at each of 2 dose levels, based on a starting dose of 200 mg bid derived from preclinical studies of sorafenib combined with radiotherapy. Since 400 mg bid is the well established MTD for sorafenib monotherapy in patients with renal cell carcinoma and hepatocellular carcinoma, the dose will not be escalated above this level even if DLT is not observed.

MTD is defined as the dose that produces dose limiting toxicity (DLT) in 33% of patients. Dose level escalation will be determined based on DLTs observed through the first 70 days of therapy, but DLTs will be monitored in the post-operative period. Dose de-

escalation may occur if excess late DLTs are observed. **See Section 7.1 for further explanation of determination of DLT.** Briefly, if 0/3 patients experience DLT, the dose will be escalated for the next cohort of 3 patients. If 1/3 patient experience DLT, the same dose will be repeated for the next cohort of 3 patients. If 2/3 or 3/3 patients experience DLT, the study will be terminated or dose reduced. Toxicity and wound complication rates will be reported.

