#### Treatment Stop Rule

A pause in study accrual will be implemented in the phase II portion of the trial after 10 patients have completed concurrent sorafenib plus conformal radiotherapy followed by surgical resection. Safety assessment will be made 6 weeks following resection of the 10th patient (9 – 13 weeks following completion of concurrent sorafenib and RT) to ensure that excess DLTs are not observed. The study will be **terminated for safety** (not lack of efficacy) if 4 of these 10 patients experience grade 3 adverse events or greater since this would represent an increase from the baseline rate of serious AEs expected from the standard combination therapy of preoperative radiation and surgical resection. This pause in accrual will allow us to review all safety data collected to date. If DLTs in excess of our stopping rule are not observed, then the phase II trial will continue to the targeted accrual of 25 patients.

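### The move from Phase I to Phase II requires no postoperative observation at the chosen dose, and late DLTs have no binding, pre-specified role before Phase II opens

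*Protocol*

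**What the plan says.** **Condition for Phase II.** The Synopsis (Rationale) states: "Enrollment into Phase I will be completed prior to the initiation of phase II". Section 3.1 adds that Phase II uses the MTD from Phase I, and section 4.0 makes Phase II enrollment depend on the Phase I result.

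**Window for escalation.** Section 7.1: "Dose level escalation will be determined based on DLTs observed from start of treatment until date of surgery". Section 4.0 agrees: "DLTs observed from initiation of sorafenib/RT until time of surgery". Section 13.1.1 differs: "Dose level escalation will be determined based on DLTs observed through the first 70 days of therapy".

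**Late events.** Section 7.1: "DLTs will be monitored in the postoperative period, and dose de-escalation may occur if excess late DLTs are observed". Section 13.1.1 repeats the substance and adds that toxicity and wound complication rates will be reported. The DLT definition in section 7.1 covers grade 3-4 non-hematologic toxicity with listed exceptions. Wound events are not among the exceptions, but the major wound complication definition in section 10.4.2 is not linked to it.

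**Wounds.** Section 1.2 cites a perioperative wound complication rate of 35% with preoperative radiotherapy, against 17% with postoperative. Section 7.5 says that "documentation of wound complications is an integral part of this clinical trial".

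**Phase II check.** The Treatment Stop Rule (sections 7.1 and 13.1.2) pauses accrual after 10 resected patients. "Safety assessment will be made 6 weeks following resection of the 10th patient", and the study is terminated if 4 of the 10 have grade 3 or greater adverse events.

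**The concern.** In Phase II the protocol treats a postoperative look, at a fixed time and with a fixed number, as necessary for judging safety. At the earlier step, where the Phase II dose is settled, it requires no such look. Major wound complications occur after surgery by definition, so most or all of the period in which they can arise lies outside the window that determines the MTD.

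As written, Phase II could open while the last Phase I patients at the chosen dose have had little or no time after surgery. If postoperative toxicity at that dose were high, the first mandatory review would come after 10 further patients had been irradiated, given sorafenib and resected. The stated action at that review is termination of the study, not reconsideration of the dose.

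**Working it through.** **1. Reproducing the protocol's own figure.** Section 7.5 puts surgery 3 to 7 weeks after the end of sorafenib/RT, and the stop rule adds 6 weeks. 3 + 6 = 9 and 7 + 6 = 13, which matches the stated 9 to 13 weeks.

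**2. Postoperative days inside the escalation window.** Let *s* be the day of surgery, about 50 to 90 (section 7.5), with day 1 the start of radiotherapy (section 7.4).

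- Sections 4.0 and 7.1 (to surgery): 0 days for any *s*.
- Section 13.1.1 (first 70 days): 70 − *s*, if positive.

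| Surgery day *s* | 70 − *s* | Postoperative days covered |
|---|---|---|
| 50 | 20 | 20 |
| 56 | 14 | 14 |
| 70 | 0 | 0 |
| 84 | −14 | 0 |
| 90 | −20 | 0 (window closes 20 days before surgery) |

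**3. When later information arrives.** A look 6 weeks after surgery falls on day *s* + 42, that is day 92 to 132, against a read-out at day 50 to 90 under section 7.1. The 120-day packing component of the section 10.4.2 definition falls at *s* + 120, that is day 170 to 210. That is outside both DLT windows and also beyond a 6-week look.

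**4. How much signal the Phase I patients could give.** Under section 7.1 a level is enrolled with 3 patients and expands to 6 only after one DLT, so a dose can be chosen on 3. With wound event rate *p*, P(2 or more of 3) = 3*p*²(1 − *p*) + *p*³.

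- *p* = 0.35 (section 1.2): 0.239 + 0.043 = 0.28
- *p* = 0.50 (assumed): 0.375 + 0.125 = 0.50
- *p* = 0.60 (assumed): 0.432 + 0.216 = 0.65

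The protocol gives no expected wound rate with sorafenib added; 50% and 60% are illustrations only.

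**5. What the Phase II check does.** Reading the rule as 4 or more of 10, the chance of stopping at a true rate *p* of grade 3 or greater adverse events is the binomial tail P(X ≥ 4 | n = 10).

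| True rate | P(stop) | Expected patients affected among the 10 |
|---|---|---|
| 20% | 0.12 | 2 |
| 35% | 0.49 | 3.5 |
| 50% | 0.83 | 5 |
| 60% | 0.945 | 6 |

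The rule detects a high rate well, but only after those patients have been exposed. It counts all grade 3 or greater adverse events, which are not the same as major wound complications under section 10.4.2.

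**The case against.** - **A reader might infer that wound toxicity has no say in the Phase II dose.** The documents do not support that. The de-escalation clause allows action on late DLTs, and a grade 3-4 wound event can fall under the non-hematologic DLT wording. What is missing is a binding, pre-specified role.
- **A reader might infer that no wound outcome at all would be known at the chosen dose.** That is the worst case. Earlier patients in a cohort may already have had surgery. A level reaches 6 patients only after a DLT in its first 3. If those 3 finish their window before the next 3 start, the second 3 need about 50 to 90 days to reach surgery, so the first 3 would then have at least about 7 weeks of follow-up. This is why the working uses 3 patients and not 6. Still, nothing requires these outcomes to be awaited or reviewed.
- **A reader might infer that sorafenib is expected to raise wound complications.** The protocol does not say so. The 35% is for preoperative radiotherapy without sorafenib, section 8.1 lists no wound-healing event, and section 7.5 calls the documentation of wound complications integral.
- **The Phase II rule is a real safeguard.** It imposes a pause and mandatory termination, with a stopping probability of about 0.95 at a true 60% rate. That stands, but it acts after 10 resections and does not inform the choice of dose.
- **The schema is not readable.** Section 4.0 refers to it, and its figures are not available here. A transition rule might be drawn there, so the finding is limited to the readable text.
- **The undefined term for excess late DLTs**, taken alone, would be only a missing detail.

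**Conclusion.** The point holds in a limited form. In the readable text, Phase II may open on completed Phase I enrollment plus an MTD drawn from a window that covers no postoperative days (sections 4.0 and 7.1), or at most about 20 (section 13.1.1). Late DLTs can influence the dose, but only by discretion. This is out of step with the protocol's own 6-week postoperative check in Phase II, which comes 10 resections later.

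The timing result rests only on the protocol's stated days. The size of the harm avoided cannot be fixed: it depends on an assumed wound rate, and with 3 patients the signal is modest (0.28 at 35%, 0.65 at 60%). The case for change is that the information would come from patients already enrolled, at little cost. It does not rest on any claim that the chosen dose will prove unsafe.

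**What to change.** Reconcile the Synopsis and sections 3.1, 4.0, 7.1 and 13.1.1 with the Treatment Stop Rule, so that the protocol states which postoperative safety data from Phase I patients at the chosen dose are reviewed before Phase II opens. The existing 6-week postoperative assessment is an available reference point. In the same amendment, reconcile the two DLT windows (to surgery, and 70 days), and state what the late-DLT clause means by excess and when it is judged. Any count, timing and action are for the clinical team to set.

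If the 6-week reference is used, the cost is an amendment and a wait of up to about 6 weeks after the last Phase I resection, with no added patients or procedures. A 6-week look would not capture the 120-day packing criterion in section 10.4.2, and the text should acknowledge this.
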